### Blinding

2.6

Given the nature of the acupuncture intervention, it is not feasible to blind participants or acupuncturists. Therefore, to minimize bias, this study will employ a single-blind (assessor-blind) design, implementing the following measures:

Blinding of Key Personnel: All outcome assessors, data managers, and statisticians will remain blinded to treatment assignment until the database is locked.Separation of Roles: Acupuncturists will not participate in outcome assessment or data management. Conversely, outcome assessors will not be involved in the intervention process to prevent unintentional bias. Acupuncturists will receive standardized training before the trial and adhere to a communication protocol with participants to avoid disclosing any group-related information.Emergency Unblinding Procedure: In the event of a serious adverse event (SAE) or other urgent medical situations where knowledge of group assignment is necessary for participant management, the principal investigator must request approval from the ethics committee. Upon approval, an independent, unblinded data administrator will perform the unblinding. The reason, time, and personnel involved in the unblinding will be fully documented. The unblinded participant will discontinue the study intervention but will continue safety follow-up. Data from unblinded participants will remain in the primary analysis according to the intention-to-treat principle.To further minimize expectancy-related bias, participants’ baseline expectations regarding acupuncture will be assessed using the Acupuncture Expectancy Scale. Expectancy scores will be included as covariates in the primary statistical analysis.To formally evaluate the success of assessor blinding, after completion of the primary endpoint assessment at Week 6 (and, if applicable, at Week 24), blinded outcome assessors will be asked to guess each participant’s treatment allocation (acupuncture or waitlist control) and to indicate their confidence level. Blinding success will be evaluated descriptively by calculating (1) the proportion of correct guesses relative to chance level and (2) Bang’s Blinding Index (BBI) with corresponding 95% confidence intervals. A BBI value close to zero will be interpreted as indicating successful blinding. These analyses are intended to assess the adequacy of blinding procedures rather than to test treatment effects.

### Interventions

2.7

#### Acupuncture group

2.7.1

In addition to their standard pharmacotherapy, participants assigned to the acupuncture group will receive a standardized acupuncture intervention. The treatment protocol consists of 18 sessions, administered three times per week over 6 weeks.

All procedures will be performed by licensed physicians with at least 3 years of clinical acupuncture experience. Prior to the trial, all acupuncturists must complete standardized training and pass an assessment to ensure procedural consistency. To ensure continuity, each participant will be treated by the same acupuncturist throughout the intervention period.

Acupoint Prescription and Needles:

The selected acupoints are: Sishenzhen(four points located 1.5 cun anterior, posterior, and lateral to GV20), Shenting (GV24), Yintang (GV29), Neiguan (PC6, bilateral), Shenmen (HT7, bilateral), and Sanyinjiao (SP6, bilateral). Please refer to **Figure 2** for the location of the related acupoints.

**Figure 2 f2:**
[figure not shown]
The location of each acupoint.

The acupoint prescription was informed by traditional acupuncture principles and supported by neuroanatomical plausibility. Sishenzhen, Shenting (GV24), and Yintang (GV29) were selected as core points to “regulate Spirit (Shen)” along the Governor Vessel. Anatomically, these scalp points overlie cortical projection areas related to the prefrontal cortex, a key region involved in affect regulation, as suggested by functional neuroimaging studies examining acupuncture-related modulation of prefrontal and affective brain networks (24, 25). Neiguan (PC6), Shenmen (HT7), and Sanyinjiao (SP6) were included based on established clinical practice to synergistically address somatic and autonomic symptoms.

Acupoint locations will follow the GB/T12346–2021 standard (“Naming and Location of Acupoints”). Disposable, sterile stainless steel needles (Tianxie brand, Suzhou Medical Instrument Factory, China; 0.30 mm × 25 mm or 0.30 mm × 40 mm) will be used.

Procedure:

Participants will be treated in a supine position. After routine disinfection of the acupoints with iodine tincture, needles will be inserted to the following depths: 10–20 mm for Sishenzhen, Shenting (GV24), and Yintang (GV29); 25–30 mm for Neiguan (PC6), Shenmen (HT7), and Sanyinjiao (SP6).

Following insertion, gentle lifting, thrusting, and twisting manipulations will be applied to elicit the deqi sensation (defined as soreness, numbness, distension, or a radiating sensation). Once deqi is achieved, all manipulation will cease. The needles will be retained for 30 minutes, during which the participant must remain still.

#### Waitlist control group

2.7.2

Participants in the waitlist control group will continue their stable, standard medication regimen for the 6-week study period. They will not receive acupuncture or any other study-specific interventions during this time. For ethical reasons, participants in the control group will be offered compensatory acupuncture treatment (using the same protocol as the acupuncture group) after the 6-week intervention period concludes.

To ensure comparability, all participants in both groups must maintain a stable antiparkinsonian medication regimen throughout the study. If any dose adjustments are necessary, they will be assessed by the investigator, documented in the CRF, and converted to the levodopa equivalent dose (LED) (26). No new systemic interventions that could potentially affect depressive symptoms will be permitted during the study. All changes in concomitant medications will be fully documented.

The use and dosage of antidepressant medications will be kept stable whenever possible throughout the 6-week controlled period. “Stable” is defined as no initiation, discontinuation, or dose change within 4 weeks prior to enrollment. During the trial, clinically indicated adjustments will be permitted for safety reasons or symptom worsening. All changes (type, dose, timing, and reason) will be documented and accounted for in the ITT analysis, with sensitivity analyses performed to assess robustness.

To monitor potential contamination during the waitlist period, at each assessment visit participants will be asked using a standardized checklist whether they have received any acupuncture or other non-study interventions for mood or motor symptoms (including acupuncture, electroacupuncture, moxibustion, rTMS, or psychotherapy) since the last visit. Any such use will be recorded as a protocol deviation (type, frequency, timing, and provider) and considered in the per-protocol and sensitivity analyses.

### Outcomes

2.8

#### Primary outcome

2.8.1

The primary outcome measure is the change in MADRS total score from baseline (W0) to Week 6 (W6) (27). The MADRS consists of 10 items (total score 0–60) and is highly sensitive to changes in depressive symptoms. Compared to the HAMD, the MADRS places greater emphasis on affective and cognitive dimensions and is less confounded by somatic symptoms (e.g., sleep, appetite, and energy levels) that overlap with PD. This makes it particularly suitable for assessing depressive improvement in patients with PD-D (28).

In addition to analyzing the change as a continuous variable, we will also use the MADRS to calculate the treatment response rate (≥50% reduction) and clinical remission rate (total score ≤10). These outcomes will be interpreted in the context of the minimum clinically important difference (MCID ≈ 2 points) to provide a comprehensive assessment of both statistical and clinical significance (29).

Beyond the primary endpoint at Week 6 (W6), follow-up assessments will be conducted at Weeks 8, 12, and 24 to evaluate the durability and trajectory of treatment effects on depressive symptoms, motor function, sleep quality, and quality of life. These follow-up outcomes are exploratory and will be analyzed descriptively and, where appropriate, using mixed-effects models similar to the primary analysis, without formal adjustment for multiple comparisons.

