### Study design

2.1

This study will be a single-center, prospective, evaluator- and statistician-blinded, two-arm, parallel-group randomized controlled trial (RCT) that will be conducted at the First Affiliated Hospital of Guangzhou University of Chinese Medicine. We will recruit 88 patients with PD-D, who will be randomly assigned in a 1:1 ratio to either the acupuncture treatment group or the waitlist control group.

All participants will maintain their stable, standard medication regimen throughout the study. A waitlist control design will be used to assess the add-on benefit of acupuncture. For ethical reasons, participants in the control group will be offered compensatory acupuncture treatment after the 6-week control period.

The study flow is illustrated in **Figure 1**, outlining the entire process from screening to follow-up. The schedule for all interventions, assessments, and follow-up visits is summarized in **Table 1**. Patients and the public were not involved in the design or conduct of this trial; however, results will be disseminated to participants in plain language after study completion.

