### Statistical analysis methods

2.10

The ITT population will include all randomized participants analyzed according to the group to which they were assigned, regardless of adherence. Missing outcome data will be handled under the MMRM framework. A per-protocol (PP) analysis will also be conducted as a sensitivity analysis, excluding major protocol deviations. All statistical analyses will be performed using SPSS Statistics version 26.0 (IBM Corp., Armonk, NY, USA).

Continuous variables will be described as mean ± standard deviation (SD) or median (interquartile range, IQR), while categorical variables will be presented as frequencies and percentages. Baseline characteristics will be compared between groups using appropriate parametric or non-parametric tests.

The primary outcome (change in MADRS score) will be analyzed using a mixed-effects model for repeated measures (MMRM). The model’s fixed effects will include group, time, and the group-by-time interaction. Baseline MADRS score, the stratification factors (baseline severity and antidepressant use), and the Acupuncture Expectancy Scale score will be included as covariates (37). To assess the robustness of the primary findings and to address potential dilution effects associated with very mild depressive symptoms, a prespecified sensitivity analysis will be conducted excluding participants with baseline MADRS scores in the very mild range (e.g., MADRS < 10). The primary analysis model will be re-run in this restricted sample.

Missing values will be assumed to be missing at random (MAR) within the MMRM framework. Sensitivity analyses will be conducted using multiple imputation and pattern-mixture models. Key secondary outcomes (treatment response and remission rates) will be analyzed using chi-square or Fisher’s exact tests. Logistic regression will be used to adjust these outcomes for covariates, and results will be reported as odds ratios (ORs) with 95% confidence intervals (CIs).

Other continuous outcomes (e.g., MDS-UPDRS III, HADS, PDQ-39, PSQI) will be analyzed using ANCOVA or MMRM. Exploratory mechanistic biomarkers will be analyzed using ANCOVA with a false discovery rate (FDR) correction. These exploratory analyses are intended for hypothesis generation only.

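### Controls are offered acupuncture after Week 6, so group contrasts at Weeks 8, 12 and 24 compare immediate with delayed treatment rather than durability, and Week 6 is the primary model's only pre-crossover visit

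*Protocol article*

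**What the plan says.** Section 2.1 states that "participants in the control group will be offered compensatory acupuncture treatment after the 6-week control period". Section 2.7.2 repeats the offer and adds that it is the same treatment: "offered compensatory acupuncture treatment (using the same protocol as the acupuncture group) after the 6-week intervention period concludes". Section 2.7.1 gives the length of that course: "The treatment protocol consists of 18 sessions, administered three times per week over 6 weeks". Neither section gives a start date for controls or an expected uptake.

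Table 1 lists post-baseline MADRS at Weeks 6, 8, 12 and 24 only. Section 2.8.1 sets the primary endpoint at Week 6 and gives the later visits their own purpose: "follow-up assessments will be conducted at Weeks 8, 12, and 24 to evaluate the durability and trajectory of treatment effects". It calls these outcomes exploratory, to be "analyzed descriptively and, where appropriate, using mixed-effects models similar to the primary analysis, without formal adjustment for multiple comparisons".

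For the primary analysis, section 2.10 says: "The model’s fixed effects will include group, time, and the group-by-time interaction". The outcome is change in MADRS, and baseline MADRS, the two stratification factors and expectancy are covariates. On missing data it says: "Missing outcome data will be handled under the MMRM framework". Missing at random is assumed, with multiple imputation and pattern-mixture models as sensitivity analyses. The section does not name the visits in the model.

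The contamination checklist in section 2.7.2 is aimed at treatment outside the study during the waiting period. Nothing in the article says how the compensatory course is handled at Weeks 8 to 24, and the limitations in the Discussion do not mention it.

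**The concern.** Durability means how much of the acupuncture effect persists relative to patients who did not have acupuncture. After Week 6 the design no longer guarantees such a group. Once controls take up the offer, the arm term compares patients treated early with patients treated late. A benefit that lasts fully can then look like a benefit that has faded, because the controls have caught up. A significant arm-by-visit interaction could arise from the crossover alone. This applies to every follow-up domain named in section 2.8.1: mood, motor function, sleep and quality of life.

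A second consequence concerns the primary model. Of the four post-baseline visits, only Week 6 precedes the offer. The protection against missing data that one expects from a repeated-measures model comes from other visits under the same treatment conditions, and here there are none.

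**Working it through.** **Inputs.** Planned difference 2.4 points, SD 6.0, 20% dropout, 44 per arm (section 2.4). Course of 18 sessions at three per week (section 2.7.1). MADRS at Weeks 6, 8, 12 and 24 (Table 1). Uptake, start date, build-up and loss of effect are not given; they are assumptions here and are shown as ranges.

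**The plan's own figures.** 2.4/6.0 = 0.40 and 35/0.8 = 43.75, rounded up to 44; both agree with section 2.4. The 35 completers do not reproduce from an effect size of 0.40 without covariate gain (99 per arm by the normal approximation). That is a separate matter and nothing below depends on it.

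**Step 1: calendar for a control starting at Week 6.** By Week 8: 2 × 3 = 6 of 18 sessions, or one third. By Week 12: all 18. At Week 24: 12 weeks after finishing, against 18 weeks for the acupuncture arm.

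**Step 2: expected difference in benefit (acupuncture minus control).**

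Difference(t) = 2.4 × [R(t) − u × G(t)]

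R is the share of benefit retained in the acupuncture arm, u is control uptake, and G is the share gained and kept by treated controls. Equal efficacy in both arms and linear build-up over the course are assumed.

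- No loss: R = 1, 1, 1 and G = 1/3, 1, 1 at Weeks 8, 12, 24.
- Half the benefit lost by Week 24 in the acupuncture arm (exponential): R = 0.5^(2/18) = 0.926, 0.5^(6/18) = 0.794, 0.5; G = 1/3, 1, 0.5^(12/18) = 0.630.

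| Loss of effect | Uptake | Week 8 | Week 12 | Week 24 |
|---|---|---|---|---|
| None | 0% | 2.4 | 2.4 | 2.4 |
| None | 50% | 2.0 | 1.2 | 1.2 |
| None | 100% | 1.6 | 0.0 | 0.0 |
| Half by Week 24 | 0% | 2.2 | 1.9 | 1.2 |
| Half by Week 24 | 50% | 1.8 | 0.7 | 0.4 |
| Half by Week 24 | 100% | 1.4 | −0.5 | −0.3 |

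The 0% rows are what a durability analysis should show. At Week 12 the departure from them is u × 2.4 whatever the loss: 2.4 − 0.0 = 2.4 and 1.9 − (−0.5) = 2.4 at full uptake. An expected difference of 0 at Weeks 12 and 24 arises from a fully durable effect with full uptake, and equally from an effect that has vanished in both arms.

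**Step 3: the primary model.** Expected losses are 44 × 0.20 = 8.8, about 9 per arm. With change as the outcome and baseline as a covariate, a visit term and its interaction need at least two post-baseline visits. The stated terms therefore either draw in visits after the offer or reduce to a single-visit analysis of covariance.

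One simulated data set (35 per arm, SD 6, correlation 0.6 between visits, no covariates, unstructured covariance, full uptake) gave these Week 6 contrasts:

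| Missing pattern | Joint model, Weeks 6–24 | Week 6 only |
|---|---|---|
| None | −0.472 | −0.472 |
| 20% lost before Week 6 | −1.013 | −1.013 |
| 20% miss Week 6, seen later | −0.448 | −0.318 |

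Only the comparison within a row is informative, since this is a single sample. The joint model adds nothing in the first two rows. In the third, scores taken after crossover enter the Week 6 estimate. The shift of 0.13 shows the mechanism; it does not measure a bias.

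**The case against.** The strongest reply is that the primary inference is untouched. The endpoint is measured before the offer, and a model with an arm-by-visit interaction gives a Week 6 contrast that equals the Week 6-only analysis whenever Week 6 is observed. That stands. A reader might infer that the primary result is contaminated, for instance by testing an arm effect averaged over four visits, which under full uptake and no loss would be (2.4 + 1.6 + 0 + 0)/4 = 1.0 instead of 2.4. The protocol does not specify such a test; it defines the primary outcome at Week 6.

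A reader might also infer that the missing-data plan has no content. That goes too far. The model conditions on baseline MADRS, the stratification factors and expectancy, and multiple imputation and pattern-mixture analyses are planned. What is absent is an intermediate score for patients lost before Week 6. An article may leave the list of modelled visits to the analysis plan, so its absence alone is not the point.

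Third, the follow-up is exploratory, may be descriptive, and acupuncture is only offered. With zero uptake the contrast does track durability, and at Week 8 with full uptake 1.6 of the 2.4 points remain. This limits size and severity. It does not rescue the contrast: under partial uptake, control treatment follows patient choice, and an exploratory label excuses the lack of multiplicity control, not a contrast that measures another quantity.

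Finally, it is tempting to say that the arms are no longer randomised after Week 6, or that the distortion can exceed the planned effect. Neither holds. The arms remain randomised to immediate versus delayed offer, which is a legitimate comparison under the right label. Under equal efficacy the Week 12 distortion is at most 2.4 points.

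**Conclusion.** The concern holds for the follow-up comparisons. A between-group mixed model at Weeks 8, 12 and 24 estimates immediate versus delayed (offered) acupuncture and cannot support a statement about durability against no acupuncture. With equal benefit of 2.4 points, controls starting at Week 6 and no loss of effect, the expected Week 12 difference runs from 2.4 at zero uptake through 1.2 at 50% to 0 at full uptake. At Week 8, with full uptake and linear build-up, it is about 1.6. Uptake and start date are unknown, so the actual distortion cannot be fixed in advance.

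For the primary analysis the finding is narrower. The Week 6 contrast is sound, but the repeated-measures model recovers nothing for patients lost before Week 6, and including later visits brings post-crossover scores into the estimate for those who miss Week 6 and return. Severity is moderate: the misdirected outcomes are exploratory, and the primary part needs clarification rather than repair.

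**What to change.** In section 2.10, state that the primary inference is the baseline-adjusted group contrast at Week 6, fitted without the later visits and with the covariates already listed. The visit and interaction terms then drop out, which also matches the analysis-of-covariance basis of the sample size in section 2.4. Keep the planned multiple-imputation and pattern-mixture sensitivity analyses.

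In section 2.8.1, reword the durability aim. Describe persistence as the acupuncture arm's within-arm change from Week 6 with confidence intervals, and say that it is uncontrolled. Label any between-group contrast at Weeks 8 to 24 as immediate versus delayed acupuncture, and report control uptake and timing descriptively beside it. Apply the same wording to the motor, sleep and quality-of-life follow-up, and add the crossover to the limitations.

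The cost is analysis text and wording; no visits or patients are added. The downside is giving up a between-group durability claim, which this design cannot support. The change should be made before database lock.

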#### Key secondary outcomes

2.8.2

To supplement the primary outcome, the key secondary outcome is the change in the Movement Disorder Society Unified Parkinson’s Disease Rating Scale Part III (MDS-UPDRS III) score (30).

The MDS-UPDRS III is an internationally recognized tool for assessing motor function in PD. It consists of 33 items with a total score ranging from 0 to 132, where higher scores indicate more severe motor impairment. In this study, it will be used to evaluate motor function improvement and perform correlation analysis with changes in MADRS scores.

All assessments will be conducted while participants are in their “ON” medication state (60–90 minutes after oral levodopa administration), and the interval since the last dose will be recorded.

#### Other secondary outcomes

2.8.3

In addition to the core outcomes mentioned above, this study will collect the following secondary outcomes to comprehensively assess the multidimensional effects of the intervention:

Hospital Anxiety and Depression Scale (HADS): This scale consists of two subscales, HADS-Anxiety (HADS-A) and HADS-Depression (HADS-D), with a total of 14 items (7 items per subscale, each subscale scored 0–21). It will be used to supplement the assessment of emotional state, as it is designed to avoid confounding by somatic symptoms (31). 39-item Parkinson’s Disease Questionnaire (PDQ-39): A PD-specific health-related quality of life measure consisting of 39 items across 8 domains. Higher scores indicate poorer quality of life. It will be used to comprehensively evaluate the intervention’s impact on quality of life (32).

Pittsburgh Sleep Quality Index (PSQI): This scale consists of 7 components with a total score ranging from 0 to 21, where higher scores indicate poorer sleep quality. It will be used to evaluate the intervention’s impact on sleep quality over the past month (33).

Patient Global Impression of Change (PGIC): A 7-point Likert scale that will be used for participants to subjectively assess the overall change in their condition, reflecting their perception of treatment effectiveness (34).

Zarit Burden Interview (ZBI): This 22-item scale (total score 0–88) will be used to assess the burden level of primary caregivers. It provides a supplementary measure of the intervention’s impact at the family level (35).

